## Abstract

**Background:**

COPD is the fourth leading cause of death in the US, and COPD exacerbations result in approximately 700,000 hospitalizations annually. Patients with acute respiratory failure due to severe COPD exacerbation are treated with invasive (IMV) or noninvasive mechanical ventilation (NIV). Although IMV reverses hypercapnia/hypoxia, it causes significant morbidity and mortality. There is strong evidence that patients treated with NIV have better outcomes, and NIV is recommended as first line therapy in these patients. Yet, several studies have demonstrated substantial variation in the use of NIV across hospitals, leading to preventable morbidity and mortality. Through a series of mixed-methods studies, we have found that successful implementation of NIV requires physicians, respiratory therapists (RTs), and nurses to communicate and collaborate effectively, suggesting that efforts to increase the use of NIV in COPD need to account for the complex and interdisciplinary nature of NIV delivery and the need for team coordination. Therefore, we propose to compare two educational strategies: online education (OLE) and interprofessional education (IPE) which targets complex team-based care in NIV delivery.

**Methods and design:**

Twenty hospitals with low baseline rates of NIV use will be randomized to either the OLE or IPE study arm. The primary outcome of the trial is change in the hospital rate of NIV use among patients with COPD requiring ventilatory support. In aim 1, we will compare the uptake change over time of NIV use among patients with COPD in hospitals enrolled in the two arms. In aim 2, we will explore mediators’ role (respiratory therapist autonomy and team functionality) on the relationship between the implementation strategies and implementation effectiveness. Finally, in aim 3, through interviews with providers, we will assess acceptability and feasibility of the educational training.

**Discussions:**

This study will be among the first to carefully test the impact of IPE in the inpatient setting. This work promises to change practice by offering approaches to facilitate greater uptake of NIV and may generalize to other interventions directed to seriously-ill patients.

**Trial registration:**

Name of registry: ClinicalTrials.gov

Trial registration number: NCT04206735

Date of Registration: December 20, 2019

Contributions to the literature
This will be among the first studies to analyze the effectiveness and feasibility of implementing interprofessional education alongside a standard of care initiative (e.g., NIV use in COPD exacerbations) as a continuing educational course onsite at hospitals.This study will add to the literature regarding the role of interprofessional education on team functionality for a standard of care initiative that can impact the use of NIV, length of patient stay, and mortality for COPD patients.

## Background

Chronic obstructive pulmonary disease (COPD) is the fourth leading cause of death in the US, and COPD exacerbations result in approximately 700,000 hospitalizations annually [1, 2]. Patients who do not respond to pharmacotherapy are placed on invasive (IMV) or noninvasive mechanical ventilation (NIV). While invasive mechanical ventilation (IMV) administered through an endotracheal tube is an effective method of treating acute respiratory, it requires treatment in an intensive care unit, and places patients at risk for a wide range of complications, including ventilator-associated pneumonia. NIV (continuous positive airway pressure, CPAP or Bilevel positive airway pressure, BIPAP) provides positive pressure ventilation via a face mask without the need for intubation. Multiple randomized controlled trials [3, 4], meta-analysis [5, 6], and analyses of real-world data [7, 8] have demonstrated that treatment with NIV, when added to usual care, reduces the risk of intubation, lowers the incidence of ventilator associated complications, and results in better short-term survival. Based on this evidence, NIV receives a grade A recommendation in current **G**lobal Initiative for Chronic **O**bstructive **L**ung **D**isease (GOLD) guidelines [9]. Furthermore, the European Respiratory Society and American Thoracic Society joint guidelines [10] as well as British Thoracic Society guidelines [11] make a strong recommendation for the use of NIV as a first-line treatment for patients with COPD exacerbation and acute respiratory failure.

Although the evidence supporting the use of NIV is compelling, prior research has demonstrated substantial variation in the use of NIV in routine clinical settings, highlighting a persistent gap in NIV adoption. In a recent study of more than 77,500 patients with COPD cared for at 400 US hospitals, median hospital percentage of NIV use among ventilated patients was 75.1% (range 9.2–94.1%) and the bottom 20% of hospitals offered a trial of NIV to less than half of ventilated patients [12]. More importantly, institutions with higher rates of NIV had lower IMV use and better clinical outcomes. Thus, low hospital rates of NIV in patients admitted for severe COPD represents an evidence practice gap and a missed opportunity to improve the outcomes among this vulnerable population. Appropriate delivery of NIV is a complex, multicomponent intervention that requires timely recognition, and effective communication, and coordination across multiple disciplines. Figure 1 depicts the flow for a patient who comes to the emergency department with severe COPD exacerbation and each clinician’s responsibilities in the process of NIV initiation and monitoring. Only few studies have tested strategies for supporting NIV implementation. A single site, before-after study from Canada found that multidisciplinary guidelines for the use of NIV in patients with acute respiratory failure (ARF) were associated with greater NIV utilization but included only patients in the intensive care unit [13].

**Fig. 1 Fig1:**
[figure not shown]
Clinician roles in management of patients with severe COPD in need for ventilation. Key: ED = [name] = Physician, RT = Respiratory Therapist, NIV = Noninvasive Ventilation, IMV = Invasive Ventilation, RT = Respiratory Therapist

For this study, we used the intervention mapping process model to develop and select implementation strategies to increase the uptake of NIV [14]. Figure 2 summarizes the steps in the development of our implementation strategy to increase the use of NIV in severe COPD exacerbation. In step 1 (formative evaluation), we conducted semi-structured interviews with key informants in a sample of hospitals with high rates of NIV and good COPD outcomes (low mortality and NIV failure rates). The analysis of the interviews revealed 3 different professional identities and roles in NIV delivery: physicians, respiratory therapists (RTs), and nurses. Although several clinicians’ tasks are distinct, Fig. 1 shows the connections between physicians, nurses, and RTs indicating the need for coordination to ensure optimal patient outcomes. The three groups encounter significant professional boundary issues with regards to their work responsibilities and priorities. For example, nurses were concerned about patient’s inability to eat or take medications while on NIV. RTs considered that nurses do not have a good understanding of the vital role of NIV. However, the two professions agreed that when there was a shared understanding of the treatment plan and when the concerns from both sides were openly addressed, the collaboration was considerably improved. RTs perceived themselves as experts in initiating and managing NIV; in some institutions, there was a strained relation between the RTs and physicians, with RTs complaining about a lack of autonomy and the need to wait for physicians when NIV was immediately indicated. We identified the following contextual factors and strategies associated with successful NIV implementation: provider buy-in, respiratory therapists (RT) autonomy to deliver NIV independently, interdisciplinary teamwork, collegial, trusting relationships between RTs, physicians, and nurses, and ongoing staff education [15].

**Fig. 2 Fig2:**
[figure not shown]
Step-by-step development and evaluation of the implementation strategy. Key: NIV = Noninvasive Ventilation, COPD = Chronic Obstructive Pulmonary Disease, RT = Respiratory Therapist, TDF = Theoretical Domains Framework, ERIC = Expert Recommendations for Implementing Change, RCT = Randomized Control Trial

In step 2, we organized the specific types of determinants that influence NIV delivery using the Theoretical Domain Framework (TDF) [16]. The TDF was used as a guiding theory for this project because the desired behavior change is primarily at the individual level, e.g., convincing providers to consider NIV in any patient with severe COPD exacerbation. We summarized the barriers in the TDF domains with an eye toward choosing an implementation strategy which could overcome several of the identified barriers. Eight of the 14 domains (knowledge, skills, professional roles and identity, beliefs about capabilities, beliefs about consequences, environmental context and resources, social influences, and emotion) were present in the existing literature and our research.

Interdisciplinary teamwork, on-going education, providers buy-in, and RTs autonomy were found as the top four determinants for successful NIV delivery in COPD exacerbations. These findings suggest that to succeed, implementation strategies need to account for the complex and interdisciplinary nature of NIV therapy and the need for team coordination.

Step 3: to guide the selection of implementation strategies, we used the Expert Recommendations for Implementing Change (ERIC) [17]. The main themes that emerged from the qualitative analysis and literature review mapped to the TDF domains and the implementation strategies most likely to address those barriers are shown in Table 1. Systematic analysis of the barriers suggested that to succeed, implementation strategies for knowledge transfer need to account for the complex and interdisciplinary nature of the NIV therapy and the need for team coordination; however, these hypotheses need to be carefully tested. Interprofessional, dynamic team training for physicians, RTs, and nurses was the implementation strategy selected as targeting several key determinants [16, 18, 19].

**Table 1 Tab1:**
[figure not shown]
Themes mapped to theoretical domain framework and implementation strategies

NIV is delivered in high acuity environments by teams in which membership is dynamic, decisions must be made quickly, and members are not always face-to-face (asynchronously taking care of patients). This creates a critical need for effective communication, conflict management, and shared mental model [20] skills that are well suited to IPE approaches [21–23]. By contrast, conventional education regarding NIV is administered to individual clinicians or groups of clinicians of the same discipline via lectures or online modules. Educating individual care providers in silos does not address the interprofessional collaboration inherent to NIV delivery. On the other hand, IPE competencies emphasize the importance of establishing awareness and knowledge regarding interprofessional team roles. In this way, leveraging an IPE platform enables learning via interaction between two or more professions who learn from, with, and about each other’s roles and responsibilities (in this case, in regards to NIV) [24, 25].

The overall objective of this study is to conduct a pragmatic, parallel, 2-arm randomized cluster trial to compare the effectiveness of two implementation strategies: on-line education (OLE) and interprofessional education (IPE) on the uptake of NIV. The central hypothesis is that IPE will outperform conventional education, and that RT autonomy and/or team functionality will act as mediators. We will accomplish this goal by completing three specific aims.

Aim 1: To compare the effectiveness of OLE and IPE for increasing the delivery of NIV in appropriate patients hospitalized with COPD exacerbation.

Aim 2: To examine the effect of OLE and IPE on RT autonomy and team functionality as potential mediators of NIV uptake.

Aim 3: To evaluate the acceptability and feasibility of the OLE and IPE strategies to inform further refinement of the strategies.

## Methods and design

### Study design

In this cluster randomized controlled 2-arm parallel trial, 20 hospitals will be randomized to OPE or to IPE. Patients and clinicians are clustered within the hospitals because the IPE encourage facility-level change in clinicians’ communication and care coordination.

### Hospital recruitment

The study will be conducted in 20 hospitals with risk-adjusted NIV proportion below median that have at least 35 eligible COPD admissions in an 18-month period. Potential eligible hospitals are those participating with data in Premier database, a voluntary, fee-supported database containing highly detailed hospital billing data pooled from more than 600 geographically and structurally diverse hospitals whose makeup closely resembles that of US hospitals. Hospitals that demonstrate interest in participating in the study will be asked to commit to form a COPD-NIV team composed of one physician, one RT, and one nurse that will be in close contact with the investigators and are responsible for delivering the educational intervention in their institution. Eligible hospitals will be contacted in a random order until the sample of 20 hospitals is achieved. To assess for potential participation bias, we will compare participating and refusing hospitals using available data such as size, ownership, teaching status, and location. The overall study design is shown in Fig. 3.

**Fig. 3 Fig3:**
[figure not shown]
Study flowchart. Key: RS-NIV = Risk Standardized Noninvasive Ventilation, IPE = Interprofessional Education, RT = Respiratory Therapist, OLE = Online Education, LOS = Length of stay

The Explanatory Continuum Indicator Summary **(PRECIS**) framework was used to assess the pragmatism of the trial (Fig. 4).

**Fig. 4 Fig4:**
[figure not shown]
The explanatory continuum indicator summary (PRECIS). Key: RS-NIV rates: Risk Standardized-Noninvasive Ventilation rates, COPD: Chronic Obstructive Pulmonary Disease, NIV: Noninvasive Ventilation, RT: Respiratory Therapist, IPE: Interprofessional Education

### Randomization

We will randomly allocate hospitals to one of the study arms, stratified by the baseline NIV proportion and hospital bed size. A researcher not involved in the study and blinded to the identity of the hospitals will use a computer-generated randomization scheme. The randomization scheme will be concealed to the investigators. Due to the character of the intervention, it will not be possible to blind participants or investigators providing the educational program; however, the investigators will not be aware of the results of the study by intervention arm until the analysis is finalized.

### Implementation strategies

The trial will compare two implementation strategies: one active control consisting of traditional, online education (OLE) learning and a strategy of in-person interactive inter-professional education (IPE). Consent for participation in the educational strategies will be sought as a waiver of consent via an email sent to all potential participants after the randomization period and prior to the implementation at each site. Participants in the COPD-NIV teams and the training will be physicians, RTs, and nurses who are involved in treating patients with severe COPD exacerbation.

The following domains will be targeted in the educational training interventions:
Knowledge: evidence for NIV use, understanding patient selection, monitoring, and weaning (NIV algorithm); NIV advantage over IMV (OLE and IPE)Skills: ability to manage/monitor patients on NIV: NIV settings, how to attend to patient comfort (OLE and IPE)Interprofessional collaboration competencies: roles and responsibilities, teams and teamwork, values and ethics, and interprofessional communication (IPE only)

The hospital-based COPD-NIV teams will be responsible throughout the trial period for encouraging clinicians from each specialty to complete the courses. The investigators will have a conference call with the COPD-NIV team after the institutions have been randomized to discuss recruitment and surveys’ delivery. (e.g., RT Autonomy, team functionality, and organizational readiness for implementing change). Conference calls between the investigators and the individual COPD-NIV team will continue every quarter for the duration of the 18 months of active implementation period with a follow-up call at the end of the study.

#### Active control group: online education (OLE)

Sites will be given access to free continuing education modules customized for each discipline; RT and nurse online education training will be approximately 30 min long, and physician’s online education training will be about 1 h. The modules will be delivered online through a secure website that will allow us to count the number of providers completing the course. We will use traditional PowerPoint presentations with embedded whiteboard animation videos. We selected an active control instead of usual care, because it will allow stronger inferences about the benefits of IPE when compared to more traditional learning approaches. The online modules will be offered for the entire period of the study for all the new staff.

#### Intervention group: interprofessional education (IPE)

It will consist of a 60-minute in-person interprofessional educational workshop.

##### Training of the facilitators

We will organized a one day in-person training for all the NIV-COPD teams. The training will consist of 2 modules: (1) NIV knowledge and skills: delivered by NIV experts and (2) IPE: delivered by an expert in IPE and team training. The didactic training regarding NIV use in COPD will include a review of the evidence supporting the benefits of NIV, advantages of NIV as compared to invasive mechanical ventilation (IMV), selection of patients, contraindications to NIV, and management of patients while on NIV including monitoring, ventilator settings, attention to patient comfort, weaning from NIV, and decision about NIV failure and need for intubation. The didactic module will emphasize the importance of early initiation of NIV in patients with severe COPD. The second half of the training will concentrate on teaching interprofessional collaboration. Specifically, the Interprofessional Education Collaborative (IPEC) recommends four key competencies in successful IPE, which include roles and responsibilities, teams and teamwork, values and ethics, and interprofessional communication [26]. We selected the following core competencies for our interactive IPE. *Professional roles and identity:* each team member learns about abilities, tasks, duties, responsibilities, and concerns of their fellows’ team members; *values/ethics*: work with individuals of other professions to maintain a climate of mutual respect and shared values; *teams/teamwork*: apply relationship-building values and the principles of team dynamics to perform effectively in different team roles to deliver patient-center care that is safe, timely, effective, and efficient [27]. Given the demands for team coordination in NIV delivery and findings in our qualitative work, we anticipate that IPE will contribute to greater RT, physician, and nurse understanding of each other’s roles, increase team communication and functionality, and stimulate the development of shared mental models which facilitate coordination for NIV. We will use positional clarification which involves verbally presenting team members with information about their teammates’ jobs through discussion [28]. Psychological safety and speaking up will be encouraged and facilitated. For example, an RT may assume that physicians have more knowledge about NIV delivery for a particular patient than they do (because physicians are generally more knowledgeable about treatments) and remain quiet; when in fact, the RT has important information about how the patient may respond (cognitive bias) [29].

The sessions will be recorded, so that participants will have ongoing access to the content. We anticipate that the members of the COPD-NIV team who will become the training facilitators at their hospital will not be subject matter experts in the training context, especially the IPE. Therefore, a special instructor script will be written and will be paired with the presentation.

##### Delivery of the IPE sessions at institutions randomized to IPE

Training sessions for clinicians at IPE sites will be led by the COPD-NIV teams and will include information (e.g., 30-min lecture), demonstration (providers will be provided with contextualized examples), and practice (30-min, action-based approach with guided practice). It will contain a scenario of a patient with severe COPD coming to the emergency room with shortness of breath. They will review the guidelines for patient selection and monitoring and NIV settings and management. Each participant will be able to try the NIV mask and understand the importance of appropriate settings and attending to patient comfort. The three core competencies for interprofessional collaboration and how they apply to the NIV delivery will be explained. The IPE sessions will be offered up to twice a month for 3 months—the number will vary by institution depending on the number of providers that need to be trained. For the entire period of the study, we will continue to have every other monthly breakfast/lunch meetings where cases of patients with COPD in need of NIV will be presented with emphasis on interprofessional work structure, RT autonomy, and team functionality. Full IPE sessions will be offered once a month every 6 months for the new staff, as part of on-boarding.

### Outcome measures

Table 2 outlines the implementation and effectiveness outcomes at the cluster (hospital) level, their implementation timing, how they will be measured, and the source of data collection.

**Table 2 Tab2:**
[figure not shown]
Outcome measures

### Analysis

#### Aim 1

To compare the effectiveness of OLE and IPE for increasing the delivery of NIV in appropriate patients hospitalized with COPD exacerbation.

##### Primary outcome

Hospital-level risk-standardized (RS) initial NIV proportion among patients hospitalized with a COPD exacerbation that were ventilated with NIV or IMV is assessed via administrative records of patients discharged from participating premier hospital who were 40 years or older and received a principal diagnosis of COPD, or a principal diagnosis of acute respiratory failure paired with a secondary diagnosis of COPD. We will use a previously validated set of ICD-10-CM codes that achieve a reasonable balance of sensitivity and specificity while minimizing potential biases [30].

##### Secondary outcomes

RS hospital rates of NIV failure (IMV after a trial of NIV), mortality, length of stay, and 30-day readmission among all patients with COPD.

All outcomes will be measured at the hospital level: (1) at baseline using prior 18 months of data, (2) at 18 months post-implementation to assess immediate/short term impact, and the following 18 months to assess sustainability. The 18-month assessment period is necessary to have adequate numbers of eligible COPD admissions for assessing hospital rates of NIV utilization. The time from randomization to the completion of the educational sessions with an expected duration of 3 months will not be included in the calculation of RS-NIV post-intervention. To examine penetration, we will measure providers’ exposure to educational training using participation logs.

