##### Noninvasive and invasive ventilation

For each patient, we will examine standardized charge codes generated daily by respiratory therapists as well as dated ICD-10-procedure codes to determine whether or not they were treated with assisted ventilation, and, if so, whether ventilation was NIV or IMV. We define the primary method of ventilation as the first method by date and distinguish between patients treated with NIV as an initial strategy from those in whom NIV use follow exposure to invasive mechanical ventilation (IMV). We have previously validated the NIV ICD procedure codes and respiratory therapy charge codes by retrospective medical chart review. Using ICD-9-CM codes alone yielded a sensitivity of 86% (95% CI, 81–92%) and specificity of 92% (95% CI, 84–98%). The approach of using ICD-9-CM procedure codes and/or respiratory therapist charges increased sensitivity to 99% (95% CI, 98–4 100%) without reducing specificity (92%, 95% CI, 84–99%) [31].

##### Statistical analysis of aim 1

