
For the secondary outcomes, our analysis will calculate hospital RS-rates of NIV failure, mortality, 30-day readmission, and length of stay among ventilated patients, as well as all COPD admissions for each study period. We will compare outcomes of OLE and IPE hospitals using models described above. Although we assume that the patients treated in IPE hospitals will have better clinical outcomes, we do not expect it to be able to detect an effect of these strategies on secondary outcomes due to overall low outcome rate, the small projected change, and relatively small number of clusters.

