The minimal number of hospitals participating in the trial was based on the analysis of Premier 2016–2017 data. Hospital RS-NIV proportions were calculated for the 457 hospitals with at least 35 eligible COPD admissions. The median RS-NIV rate among this group of hospitals was 82% (IQR 74–86%). We then selected the 48 hospitals with RS-NIV proportion less than 55%, based on the clinical impression that these hospitals would have sufficient room for improvement, as potentially eligible sites. Among these hospitals, the median number of eligible COPD patients was 197 over a 12-month period, ranging from 23 to 556 patients. The number of ventilated patients per hospital ranged from 7 to 163, with a median of 37. To achieve stability in estimation of hospital level RS-NIV, we will assess our primary endpoint at 18 months post-intervention expecting a minimum of 10 ventilated patients per hospital in which to assess NIV rates. Power analysis was conducted to determine the number of hospitals needed to assess the primary outcome of difference between the study arms in change in the hospital level risk-standardized proportion of ventilator starts that are NIV (RS-NIV). Using a type I error rate of 0.05, and standard deviation of change in rates over time derived from our prior work with the Premier data base, a total sample of 20 hospitals, 10 in each arm will give 80% power to detect difference of 15% in change (e.g., 5% increase among OLE hospitals, vs. 20% increase among IPE hospitals). Power is > 90% to detect a 20% difference in change between the intervention groups.

#### Aim 2

To examine the effect of OLE and IPE on RT autonomy and team functionality as potential mediators of NIV uptake.

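### NIV failure counts only intubation after NIV, so deaths on NIV without intubation are non-events, and no planned rate shows them among NIV-first patients

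*Protocol article*

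**What the plan says.** The Secondary outcomes section lists "RS hospital rates of NIV failure (IMV after a trial of NIV), mortality, length of stay, and 30-day readmission among all patients with COPD". The bracket is the only definition of NIV failure in the article. Death is not part of it, and no rule is given for a patient who dies on NIV without IMV.

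Statistical analysis of aim 1 gives the populations: "our analysis will calculate hospital RS-rates of NIV failure, mortality, 30-day readmission, and length of stay among ventilated patients, as well as all COPD admissions". NIV failure and mortality are therefore separate risk-standardized hospital rates. Neither is stated for patients who began on NIV.

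That group can be identified. The section on noninvasive and invasive ventilation says "We define the primary method of ventilation as the first method by date and distinguish between patients treated with NIV as an initial strategy", using dated procedure codes and respiratory therapy charges.

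On what to expect from these outcomes, Statistical analysis of aim 1 says "we do not expect it to be able to detect an effect of these strategies on secondary outcomes due to overall low outcome rate". It also assumes that patients in IPE hospitals will do better clinically. The Background treats a low NIV failure rate, alongside low mortality, as a mark of a well-performing hospital.

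**The concern.** Both arms promote NIV, and the hypothesis is that IPE will increase its use more. The facilitator training for IPE covers "weaning from NIV, and decision about NIV failure and need for intubation", and the RT autonomy section expects therapists to speak up for NIV in place of intubation. The strategies may therefore influence whether and when a patient on NIV is intubated, which is the event that the failure rate counts.

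An outcome that counts only intubation falls when fewer patients on NIV are intubated, whatever then happens to them. It cannot distinguish patients who recovered on NIV from patients who died on it. Since the article reads a low rate as good, a fall under IPE would probably be reported as benefit. At stake is the reading of one secondary outcome, not the primary comparison.

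**Working it through.** The article states no figure for NIV failure, so there is no figure to reproduce. The check takes three steps.

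**1. What the definition counts.** A patient whose first ventilation is NIV ends in one of three states:

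- later IMV: counted as NIV failure;
- no IMV, discharged alive: not counted;
- no IMV, died in hospital: not counted.

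The second and third states are treated alike. This is true whichever denominator is used for the rate.

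**2. Whether planned mortality separates them.** Among ventilated patients, let p be the proportion starting on NIV, and let m_N and m_I be mortality in NIV-first and IMV-first patients. The planned rate is

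M = p·m_N + (1 − p)·m_I.

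If p moves to p′ and m_N to m_N′, with m_I held fixed for simplicity,

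M′ − M = p′(m_N′ − m_N) − (p′ − p)(m_I − m_N).

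The trial aims to raise p; its power example is a 20-point rise under IPE against 5 under OLE. If m_I exceeds m_N (an assumption), the second term lowers M as p rises, so M can stay flat or fall while mortality among NIV-first patients rises. The rate over all COPD admissions dilutes the signal further with patients who were never ventilated. The deaths are recorded, but neither rate shows them as an outcome of starting NIV.

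**3. Illustration of size (all rates assumed).** Let f be the percentage of NIV-first patients later intubated and d the percentage who die without IMV. The rate as defined is f, the composite is f + d, and the share of composite failures left out is d/(f + d).

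| f | d | f + d | d/(f + d) |
|---|---|---|---|
| 10% | 2% | 12% | 17% |
| 10% | 8% | 18% | 44% |
| 15% | 5% | 20% | 25% |
| 20% | 2% | 22% | 9% |
| 20% | 8% | 28% | 29% |

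Now suppose f falls from 15% to 12% while d rises from 3% to 6%:

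- rate as defined: 15% → 12%, an apparent improvement of 3 points;
- composite: 15 + 3 = 18% → 12 + 6 = 18%, no change;
- deaths without IMV: 3% → 6%, doubled.

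The defined rate improves and the composite is flat. Only the separate death component shows the shift.

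**The case against.** The strongest reply is that the deaths are not lost. Mortality stands beside NIV failure in the same sentence and is analysed separately, including among ventilated patients. Keeping intubation and death as distinct endpoints and reading them together is a legitimate choice. That stands as far as it goes, and a reader should not infer that the trial ignores these deaths. It does not close the gap, because neither mortality population is the NIV-first group.

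Other parts of the reply also stand:

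- The low-power caveat, "we do not expect it to be able to detect an effect of these strategies on secondary outcomes", covers NIV failure as much as mortality. It cannot be used to dismiss one and not the other.
- The arm-specific hazard is conjecture. The Implementation strategies section gives the teaching on the advantage of NIV over IMV to both arms; only the collaboration content is specific to IPE. Nothing in the article shows that deaths without intubation would rise under IPE.
- A composite alone would be a poor substitute, because it hides an exchange of intubations for deaths, as the last example shows.
- Deaths without IMV will include deaths under treatment-limitation orders and deaths after weaning from NIV. The patient variables listed in the article include none for treatment limitation.

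It may also be said that the handling of death as a competing event belongs in a full protocol or analysis plan that is not shown. Such a document may well address it. The point here, however, concerns a definition that the article itself states, not a detail that it omits.

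**Conclusion.** The point holds as a limited one about a secondary outcome. As defined, NIV failure omits in-hospital deaths without IMV, a lower rate could partly reflect them, and the planned mortality rates do not isolate them among NIV-first patients. The primary outcome, the initial NIV proportion, is unaffected.

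The size is unknown. The 9–44% range rests on assumed rates and shows only that the omitted share need not be negligible.

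Two stronger readings are tempting and unsupported. A reader might take NIV failure to be the trial's main safety outcome; the article labels no outcome as safety and does not rank the four secondary outcomes. A reader might also say that a patient who dies on NIV is scored as an NIV success; no success category exists, and the patient is simply not counted as a failure.

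**What to change.** Among patients whose first ventilation by date is NIV, report by arm and study period:

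- (a) IMV after NIV, the present definition;
- (b) in-hospital death without IMV;
- (c) the composite of (a) or (b).

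State that a change in (a) will not be interpreted without (b), and that (c) will not be shown without its components.

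The cost is a few lines of definition and two extra table rows. Dated ventilation codes and mortality are already planned from the Premier records; the fix assumes that in-hospital death can be identified there for each patient. The downside is that (b) and (c) will include some deaths under treatment-limitation orders or after weaning. Showing the components separately keeps (a) free of these deaths but does not identify them within (b), so the report should say so.
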